### Outcomes

The following feasibility study outcomes will be measured:
Recruitment rate and follow-up rate at 3, 6, 9 and 12 monthsPatient participant preferences for paper/online/telephone versions of the outcome data collection tools, number and type of reminders required and data completeness. Measured using self-completion questionnaires at recruitment and follow-up.Patient participant, OT, CP, employer and commissioner experiences of the ROWTATE intervention and of returning to work (or not); factors facilitating or hindering engagement with the intervention or return to work; perceived appropriateness of timing of return to work; mechanisms considered important in determining key outcomes; importance and acceptability of outcome measures; acceptability of trial procedures; information on the employing organisation and its policies and practices to support return to work; potential improvements to the ROWTATE intervention; policy drivers for commissioning vocational rehabilitation, and service quality factors and contracting issues of importance. Measured using semi-structured interviews 1–12 months post patient participant recruitment.Identification of potential contamination issues. Measured by completion of contamination and mentoring records throughout the intervention period.Fidelity of and contextual and process issues related to intervention delivery. Measured by completion of intervention delivery CRFs, observations of OT and CP contacts with patients, assessment of communication skills, review of clinical records, completion of mentoring records 0–12 months post patient participant recruitment.OT and CP readiness to deliver the ROWTATE intervention following training and potential improvements to training. Measured using self-completion questionnaires (Evidence-Based Practice Confidence Scale, Evidence-Based Practice Attitude Scale and bespoke questions on confidence to deliver intervention components) before and immediately after training. Readiness to deliver the ROWTATE intervention will be measured using semi-structured interviews 1–6 months post patient participant recruitment. Competence to deliver the ROWTATE intervention will be measured by a TOSCE, plus an individual task (letter to an employer) and team-completed task (completion of clinical summary) immediately after training.Patient participants’ views on trial recruitment and retention strategies, preferences, and barriers and facilitators to trial recruitment and retention. Measured by focus groups and/or interviews 1–6 months after patient participant recruitment.

### Sample size

We will recruit 40 patient participants to take part in the feasibility study and receive the intervention. Sample sizes of 40–50 participants in total have been recommended for feasibility studies [64] and we consider 40 participants will enable us to address objectives 1 to 3.

To address objectives 2, 3, 4 and 6, we will conduct 10 case studies, including interviews with patients taking part in the feasibility study and receiving the intervention (*n* = 10) and their linked professionals (up to 40 in total), review OT and CP records of their care, and conduct observations of clinical contacts (up to 6 patient participants, with a maximum of 18 observations across the 6 patient participants). To address objective 5, all OTs and CPs delivering the intervention will complete pre and post training questionnaires, the TOSCE and the individual- and team-completed tasks.

To address objective 7, we will conduct focus groups and/or interviews with up to 22 patients who did and did not participate in the feasibility study. We anticipate this will allow ‘theoretical sufficiency’ [65] as opposed to data saturation, but further interviews will be conducted if we do not achieve theoretical sufficiency. Using ‘conceptual depth criteria’, we will look for range, complexity, subtlety, resonance and validity in the data [66].

### Adverse events

This is a non-pharmacological intervention study in a population likely to have repeated contacts with the healthcare system including hospital admissions related to their original injury. Serious and unexpected adverse events in relation to participating in this study are likely to be rare events. Consequently, the risks of patient harm arising from a low-risk intervention must be weighed against collecting large amounts of data on unrelated events. For the purposes of this study we define adverse events as hospital admissions and workplace accidents requiring medical attention. We will also collect data on ‘potential harms’ including workplace accidents not requiring medical attention and ‘near miss’ accidents. Data on adverse events and potential harms will be collected prospectively using specific patient participant completed reports and by reporting events on follow-up questionnaires. Adverse events and potential harms will also be reported by OTs, CPs and researchers who have contact with patient participants. Adverse events and potential harms will be reviewed and monitored by a subgroup of the programme steering committee.

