## Background

Injuries adversely affect working-age adults; they are the leading cause of death amongst 15–29 year olds and the second leading cause of death amongst 30–49 year olds worldwide [1]. In England and Wales in 2016, they were the third leading cause of death between 15 and 64 years of age (10,700 deaths) [2]. In 2015–2016, they resulted in more than 700,000 hospital admissions in England amongst those aged 16 and 69 years [3].

Significant concerns about survival rate post-injury [4, 5] resulted in the establishment of 22 major trauma centres (MTCs) for adults across the UK in the last decade. Patients with at least moderate trauma (injury severity score > 8) are now transported directly to MTCs. Survival rates have since improved [6], but many survivors experience physical and psychological problems [7, 8], reduced quality of life (QoL) [9] and difficulty returning to work [10, 11], with psychological and occupational needs frequently being unmet [12]. The detrimental effects of being out of work on health, healthcare resource use and wider society are well documented [13, 14]. We recently found that one third of patients admitted to hospital with an injury had not returned to work 1 year later, with many suffering significant physical and psychological problems which reduced the likelihood of returning to work [15, 16].

Moderate or severe traumatic injury often involves multiple physical injuries, affecting several body regions, frequently with psychological and/or cognitive problems impacting on work ability. These patients can face specific challenges in returning to work such as anxiety, depression and PTSD resulting from the injury [15, 17–20], pain [21], cognition problems [22], fatigue [23] and other hidden disabilities (e.g. urological problems following pelvic fracture) [24]. One year post injury, around one third of trauma centre patients report depression and PTSD [25], 22% of patients with musculoskeletal injuries report moderate or severe pain [26], just over one third of patients with traumatic brain injury report fatigue [23], and around half of patients with mild traumatic brain injury report cognitive problems [27].

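### The stated adverse event definition leaves out deaths and self-harm that involve no hospital admission or workplace accident, and nothing else in the section requires them to be reported

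*Protocol article*

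**What the plan says.** The Adverse events section of the protocol article sets a study-specific definition: "we define adverse events as hospital admissions and workplace accidents requiring medical attention". It has two items and no wording that leaves the list open. The reason given is that this is a low-risk, non-drug intervention in a "population likely to have repeated contacts with the healthcare system including hospital admissions related to their original injury", so that the risk of harm "must be weighed against collecting large amounts of data on unrelated events".

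A second class, potential harms, is open-ended, "including workplace accidents not requiring medical attention" and near misses.

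The data are to be "collected prospectively using specific patient participant completed reports and by reporting events on follow-up questionnaires". A staff route is added: "Adverse events and potential harms will also be reported by OTs, CPs and researchers who have contact with patient participants". On oversight, "Adverse events and potential harms will be reviewed and monitored by a subgroup of the programme steering committee".

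Death appears in the article only as injury epidemiology in the Background. Self-harm and suicide are not mentioned. The Background does say that, one year after injury, "around one third of trauma centre patients report depression and PTSD". Under Intervention, occupational therapists (OTs) screen for mental health problems and refer patients to a clinical psychologist (CP) where needed. Anxiety, depression and post-traumatic stress are measured at baseline and at each follow-up (Data to address objective 1).

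**The concern.** A definition stated this plainly decides what is collected, reported and reviewed. If it is followed to the letter, two of the gravest events that could befall a participant fall outside it whenever no admission or workplace accident is involved. The population carries a recognised burden of psychological illness, and part of the intervention is aimed at that burden. One would therefore expect the safety definition to have a place for the most serious psychological outcome, and for death.

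At stake is whether the steering committee subgroup is sure to see such an event. Its remit is worded in terms of the two defined classes, so an event that belongs to neither has no assured route to it. A second consequence concerns the feasibility results: a death would sit among the non-retained and could be read as a failure of follow-up.

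**Working it through.** The point turns on wording, and the article states no adverse event rate to reproduce. The check is to take each kind of event through the definition, the reporting routes and the analysis.

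**Step 1: the definition**

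| Event | Adverse event as defined? | How it enters |
|---|---|---|
| Readmission for the original injury | Yes | As an admission |
| Self-harm leading to admission | Yes | As an admission |
| Death during an admission | The admission counts | Death has no category of its own |
| Workplace accident needing medical attention | Yes | As a workplace accident |
| Self-harm managed without admission | No | Only if someone treats it as a potential harm |
| Death with no admission or workplace accident | No | Only if someone treats it as a potential harm, or as a reason for withdrawal |

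The last two rows are the gap.

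**Step 2: the reporting routes**

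- Patient-completed reports and follow-up questionnaires cannot record the patient's own death.
- OTs, CPs and researchers can learn of a death or of self-harm, but what they are asked to report is the same two classes, adverse events and potential harms.
- Potential harms is an open list, so it permits other events. The examples named are workplace accidents and near misses, and nothing directs staff to enter death or self-harm there.
- The subgroup reviews those two classes.

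Each route therefore allows the missing events to be captured, and none requires it.

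**Step 3: the analysis**

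Statistical analysis defines retention as the number giving return-to-work data on the questionnaires at 3, 6, 9 and 12 months. A participant who has died gives none from then on and so counts as not retained. Feasibility assessment criteria then sets a limit on loss to follow-up at 12 months without saying how deaths are treated. With the planned 40 participants, one death moves the 12-month retention figure by 1/40 = 2.5 percentage points. That is the effect of one death on the retention figure; it is not an estimate of how many deaths to expect.

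The same section promises the numbers and reasons for withdrawal and a participant flow chart. A death could come to light there, but as participant flow and not as an event for safety review.

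**The case against.** The strongest reply is that a journal article condenses a longer protocol. The section already speaks of serious and unexpected events related to participation, so a separate procedure for serious events may exist, and the design of the event form is properly left to it. Staff are also well placed to hear of a death or of self-harm: the OT is case coordinator over a period of up to 12 months and screens for mental health problems. Self-harm with admission, and death in hospital, do enter as admissions.

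Much of this stands, and it limits the point. It does not remove it, because the definition is something the article states outright, and any fuller procedure would have to be reconciled with it.

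A reader might infer several stronger things, which the documents do not support:

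- **That the section contradicts itself by counting every admission.** It says that harm is to be weighed against the burden of unrelated data, not that such data must be avoided. Collecting all admissions and leaving judgement to the subgroup is a defensible result of that weighing.
- **That the study is blind to deaths.** Staff reports, the open list and the withdrawal reasons are all possible routes.
- **That the same definition will be used in the definitive trial.** Nothing in the article says so.
- **That the sample size or the tolerated loss to follow-up measures the defect.** Loss to follow-up concerns questionnaire data, while staff report separately; and the precision available from 40 people would be the same under any definition. The prevalence of depression and PTSD is likewise not a rate of self-harm.

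**Conclusion.** The concern holds in limited form. As written, the definition excludes deaths and self-harm episodes that involve neither an admission nor a workplace accident, and it gives death no category of its own. Other provisions may catch these events but do not oblige anyone to report them or to put them before the subgroup.

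No frequency can be attached, since the article gives no rate for either event, and in 40 participants there may be none. The weight of the point comes from the gravity of the events and the low cost of naming them. It rests on two assumptions: that the stated definition is applied literally, and that no separate serious-event procedure in the full protocol, which is not shown, already covers these events. If one does, the remaining task is to bring the published definition into line with it.

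**What to change.** 1. Add two items to the events that OTs, CPs and researchers report and that the steering committee subgroup reviews: death from any cause, and self-harm that becomes known to the study team, whether or not there was an admission.
2. In the flow chart, show deaths at each follow-up point separately from other loss to follow-up, and say how they are treated in the 12-month loss criterion.
3. Optionally, because admissions for the original injury are expected, record whether each admission was planned and have the subgroup classify its relatedness. This is a refinement and does not correct an error.

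The cost is two further categories on the event form, one more line in the flow chart and a small extra reporting burden on staff. If the option is taken, each admission also needs two more fields. The change concerns recording and oversight only; it does not alter the intervention, the sample size or the other outcomes.

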### Data management

All study data will be handled confidentially. Participants will be assigned a unique identity code number for use on CRFs, other study documents and electronic databases. Paper records will be stored in locked cabinets and electronic records on password-protected databases. Identifiable data will be stored separately from non-identifiable data.

Quantitative data will be entered into a bespoke access database by members of the research team. Data will be checked by a member of the research team who did not complete the original data entry. Qualitative data will be anonymised and managed using the NVivo software (Version 12).

### Statistical analysis

Recruitment and retention in the feasibility study will be shown using the flow chart from the CONSORT 2010 statement: extension to randomised pilot and feasibility trials [67], adapted to include only the intervention arm. Reasons for ineligibility and for non-participation will be reported.

The recruitment rate and retention rate (number providing data on return to work on follow-up questionnaires at 3, 6, 9 and 12 months) and 95% confidence intervals will be calculated. The numbers and reasons for study withdrawals will be reported, as will patient participant preferences for questionnaire administration methods and reminders required.

Data completeness for outcome measures will be reported as frequencies and percentages for single item questions and the mean number of items (and standard deviation (SD) or median and interquartile range as appropriate) completed for scale measurements.

Frequencies and percentages will be reported for the number and content of intervention contacts, potential contamination issues identified and for demographic details, qualifications and work experience for OTs and CPs. We will sum item-level responses on the 4 EPIC questions to create a mean summary score [55]. EP-BAS total scale and sub-scale scores will be reported using means and SDs [56]. The mean (and SD) confidence in delivering the ROWTATE intervention for each item and across all items will be reported. Means and SDs for sub-scale scores for the Maastricht MAAS—Global Rating List for Consultation Skills [54] will be reported.

Using an observational checklist at the time of the TOSCE, predetermined tasks for each therapist, based on communicating the case history, discussing the clinical case, identifying pertinent questions and generating a clinical formulation will be independently rated by two researchers and assessed for agreement. Each therapist is identified by a letter, e.g. A, B or C on the observational checklist. Where a task is led by one therapist, the independent raters use the checklist to mark this lead individual as well as the cooperative interaction of the remaining two therapists on whether the pre-determined individual behaviour is not attempted, is attempted but not appropriate or attempted and appropriate. For example, task one requires the lead therapist ‘A’ to communicate the baseline questionnaire data related to the case study and the other two therapists ‘B’ and ‘C’ should interact and ask questions, clarify points to demonstrate a team approach. Findings from the TOSCE will be reported elsewhere. A written clinical formulation produced by the clinical team (two OTs and a CP from each site) and letters to the employer produced by each team member will be assessed against a model answer. Overall scores for each therapist, based on their knowledge of the intervention process (40%), clinical reasoning (50%) and written communication (10%) will be mapped to a rubric identifying the therapists as highly competent (≥ 70%), competent (50–69%) or needing additional support (≤ 49%).

Quantitative data will be analysed using SPSS v25.

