### Data collection

#### Data to address objective 1

Data will be collected to describe baseline characteristics of the study sample and of a range of outcome measures including work outcomes, health status measures and health and social care resource use data that may be suitable for use in the subsequent randomised controlled trial and its economic evaluation.

The following baseline data will be collected from patient participants at recruitment to the study using self-completed questionnaires:
Demographic detailsInjury detailsEmployment or education details (before injury and since injury)Health and wellbeing since injury: quality of life (EQ-5D-5L) [42]; Trauma Outcome Profile (pain, physical and mental function, social interaction, body image, satisfaction) [43]; depression, anxiety, (Hospital Anxiety and Depression Scale (HADS [44]) and post-traumatic stress (Impact of Event Scale (IES) [45]); recovery expectations [46]Work since injury: Return to Work Self Efficacy Scale [47], single-item question from the Work Ability Index [48] and the Work Limitations Questionnaire [49], bespoke questions on support received to return to workFinancial impact: 5 items from the Chronic Stress scale [50] and 2 items from the Family Transitions Project [51]Health and social care resource use since injury using bespoke questions designed to collect health economic data including use of secondary care, primary care, other community-based services, social care and informal care

Follow-up data will be collected from patient participants 3, 6, 9 and 12 months after recruitment by self-completion questionnaire and will comprise the same data collected at baseline excluding demographic and injury details and employment or education details before injury. In addition, following recommendations from our patient and public involvement group, the follow-up questionnaire will include the Purpose in Life scale [52]. To thank them for their time, participants will receive a £10 gift voucher for each completed questionnaire. Two reminders (paper, phone, text, online) will be used to increase response rates. Researchers will assist participants requiring help to complete questionnaires.

#### Data to address objective 2

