Follow-up data will be collected from OTs and CPs immediately after training by self-completion questionnaire and will comprise 4 items from the Evidence-Based Practice Confidence (EPIC) Scale [55], the Evidence-Based Practice Attitude Scale (EB-PAS) [56] and bespoke questions on confidence in delivering the ROWTATE intervention. Qualitative data on readiness to deliver the ROWTATE intervention will be collected from case study interviews with OTs and CPs (described in “Data to address objective 2” section above). Quantitative data on OT and CP competency to deliver the ROWTATE intervention will be collected by a team objective structured clinical examination (TOSCE) at the end of the training session, together with an individual and a team written task. The TOSCE is situated around a case study using a professional actor for the OTs and CPs to interact with. The individual written task is a letter to the employer, and the team written task is a clinical summary and formulation for the proposed intervention based on the case study. Competency results will be provided to the OTs and CPs by the training team and used by the mentors to support intervention delivery.

#### Data to address objective 6

Case study interviews (described in “Data to address objective 2” above) will be used to evaluate the importance and acceptability of outcome measures.

#### Data to address objective 7

Case study interviews (described in “Data to address objective 2” above) will be used to identify factors that may affect the running of the definitive trial. Focus groups or interviews in the qualitative study with feasibility study patient participants, plus patients who declined to participate in the feasibility study, will explore views on trial recruitment and retention strategies, preferences, and barriers and facilitators to trial recruitment and retention.

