The strengths of our study are that it builds on previous work developing and testing the feasibility of delivering a complex intervention to facilitate return to work in patients with acquired brain injury and stroke [60, 61]. It is being undertaken in two study centres with diverse patient populations, differing geographies and service configurations, allowing exploration of context-specific factors that may influence running of the definitive trial. We will evaluate OT and CP competence to provide the intervention using a TOSCE. This is particularly relevant to our intervention where OTs and CPs need to work closely together to provide coordinated vocational rehabilitation, and the TOSCE will allow us to assess inter-professional teamwork competencies [70]. There are a number of challenges we are likely to face. The study population is a heterogeneous group in terms of injury types, mechanisms and severity. This will increase the generalisability of our findings to the population of injured patients, but recruiting and retaining participants with some injuries may be more difficult than others. For example, recruiting and retaining patients with brain injuries can be difficult [71]. Data is being collected on a wide range of outcome measures, which may be burdensome for some participants. Consequently, the number of outcome measures used in the definitive trial may need to be reduced. We plan to explore barriers and enablers to recruitment and retention amongst those who did take part in our feasibility and received the intervention and those who did, but we recognise it may be difficult to recruit this latter group of patients.

The feasibility study protocol described in this paper forms part of a National Institute for Health Research Programme Grant for Applied Research. If feasibility is demonstrated, the definitive RCT will commence recruitment in 2021.

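### Reporting scale completeness only as items completed does not reliably show how many participants have a usable score

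*Protocol article*

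**What the plan says.** The Statistical analysis section of the protocol article fixes two different completeness summaries:

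- Single items are summarised at participant level: "Data completeness for outcome measures will be reported as frequencies and percentages for single item questions".
- Multi-item scales are summarised at item level: "the mean number of items (and standard deviation (SD) or median and interquartile range as appropriate) completed for scale measurements".

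Data completeness is part of objective 1 (Objectives). Most of the health and work measures listed under Data collection are multi-item instruments, for example the "Hospital Anxiety and Depression Scale". The sample is fixed under Sample size: "We will recruit 40 patient participants to take part in the feasibility study and receive the intervention".

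Three other places bear on the point:

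- Retention is defined by one variable, the "number providing data on return to work on follow-up questionnaires at 3, 6, 9 and 12 months".
- The Discussion notes that the questionnaire may be burdensome and that "the number of outcome measures used in the definitive trial may need to be reduced".
- For objective 6, case study interviews "will be used to evaluate the importance and acceptability of outcome measures".

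None of the Feasibility assessment criteria refers to scale completeness.

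**The concern.** A definitive trial needs to know what share of participants will yield an analysable score on each candidate measure at each time point. A mean or median of items completed answers a different question. It can merge two patterns that call for different action: some people skipping a whole scale, which may signal burden and argue for dropping it, and many people skipping one item, which may signal a poor item and argue for rewording it.

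The article does not simply leave this to a fuller document. It names the statistic for scales, and the statistic is less informative than the participant-level one it names for single items. Retention does not fill the gap, because someone who answers the return-to-work question and leaves a scale blank still counts as retained.

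**Working it through.** The plan gives no completeness figure to reproduce, so the check asks whether the planned summary determines the number of participants with a usable score.

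**Inputs.** n = 40 comes from Sample size. Scale length is not given in the article, so 14 items is an illustrative assumption (7 and 25 were also tried). Scoring rules are not given either, so two are used as assumptions: all items required, or at least 80% of items (0.8 × 14 = 11.2, so 12 or more).

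**1. Mean alone.**
- Pattern 1: 36 people complete 14 items and 4 complete none. Mean = 36 × 14 / 40 = 12.6.
- Pattern 2: 24 complete 13 and 16 complete 12. Mean = (312 + 192) / 40 = 12.6.

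Fully complete: 36/40 (90%, Wilson 95% CI 77% to 96%) against 0/40 (0% to 9%). The mean cannot separate these, but the planned SD does: 4.25 against 0.50.

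**2. Mean and SD together.**
- Pattern A: 38 people complete 13 items and 2 complete 1. Total = 494 + 2 = 496. Sum of squares = 38 × 169 + 2 × 1 = 6424.
- Pattern B: 29 complete 14, 10 complete 8 and 1 completes 10. Total = 406 + 80 + 10 = 496. Sum of squares = 29 × 196 + 10 × 64 + 100 = 6424.

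For both, the mean is 496/40 = 12.4 and SD = √[(6424 − 496²/40)/39] = √(273.6/39) = 2.65.

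| | Pattern A | Pattern B |
|---|---|---|
| All items completed | 0/40 (0%) | 29/40 (72.5%) |
| At least 12 of 14 items | 38/40 (95%) | 29/40 (72.5%) |

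The reported mean and SD are identical, and which pattern looks better reverses with the scoring rule.

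**3. How loose the limits are.** Linear-programming bounds on the share of participants, at a mean of 90% of items:

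| Scale and summary | All items | At least 80% of items |
|---|---|---|
| 14 items, mean 12.6 only | 0% to 90% | 53% to 100% |
| 14 items, mean 12.6, SD 2.1 | 0% to 69% | 58.5% to 98% |
| 7 items, mean 6.3, SD 1.05 | 43% to 68% | 66% to 98% |

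The SD narrows the range without closing it. Results for 25 items resemble those for 14; the all-items range is narrower for 7.

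**4. Median and IQR.** With 40 values, the lower quartile lies between the 10th and 11th ordered values under the usual definitions. If nine people leave the scale blank and 31 complete it, the 10th and 11th values are both full. The median and both quartiles then equal 14, exactly as if all 40 had completed it. Nine is the largest number that can be hidden this way: 9/40 = 22.5%. In the same data the mean would be 31 × 14 / 40 = 10.85 of 14, so the loss is hidden only if the median and IQR replace the mean. This assumes 40 people contribute; with fewer, the hidden share is still just under a quarter.

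**The case against.** The strongest reply is that the plan pairs the mean with its SD, and the SD separates the simplest contrasts, as step 1 shows. Patterns A and B were found by searching for a match. They prove that the summary is not unique, not that a misreading is likely. That is fair, and it limits the point to reliability. It does not remove it: the bounds in step 3 stay wide at an ordinary SD, and the median and IQR would tend to be preferred when counts are skewed, which is what whole-scale skipping produces.

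A second reply is that scoring rules, denominators and table layout normally sit in a fuller protocol or analysis plan, which is not shown. Their absence is not held against the article here. The point concerns the summary that the article itself names.

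Two stronger readings are tempting and should be resisted.

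- A reader might infer that the planned summary cannot guide which measures to drop. The documents do not support this. A low mean would still flag a poorly completed scale, the Discussion gives burden as the reason for reducing the number of measures, and the interviews address importance and acceptability. No feasibility criterion depends on scale completeness.
- A reader might infer that a scale with a high mean could be largely unscorable. With 20 items and 5% random item non-response, for example, the mean is 19 items but only 0.95^20 = 36% of people have every item. That figure applies only if all items are required. Under an assumed 80% rule, 99.7% would be scorable. The documents state no rule, so neither figure describes an instrument in this study.

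**Conclusion.** The point holds as a reporting weakness of modest importance. The planned summary for scales does not determine, and can seriously obscure, the number of participants with a usable score, and the article names no other summary that supplies it. The possible size is shown by 0/40 against 29/40 fully complete at the same mean and SD, and by up to 22.5% blank scales behind a full median and IQR. The first depends on an assumed 14-item scale; the second needs only n = 40 and the choice of median and IQR. All are illustrations of what could be hidden, not forecasts of what will occur.

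The consequence is that evidence for objective 1, and for choosing the definitive trial's measures, is weaker than the collected data would allow. No progression decision rests on it alone.

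**What to change.** For each scale and each time point (baseline, 3, 6, 9 and 12 months), report:

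- the number and percentage of participants with a scorable scale under that instrument's own missing-item rule, (a) out of all participants due a questionnaire and (b) out of those returning one;
- the percentage leaving the whole scale blank, with its denominator stated.

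Keep the mean (SD) or median (IQR) of items completed as a secondary description. This brings scales into line with the participant-level reporting already planned for single items.

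The cost is a few extra table rows and a note of each instrument's scoring rule. Data collection is unchanged, and the rows can be produced from the questionnaire data already planned for entry.
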